#### Pathology Examination

All lymph nodes will be placed into cassettes. Nonsentinel lymph nodes (including blue stained lymph nodes found afterwards) will undergo classic pathologic analysis (longitudinal bivalve section). If lymph nodes have a size of less than 4 mm, they will be loaded unsectioned into the cassette. Conversely, blue sentinel lymph nodes and all fluorescent lymph nodes (found to be fluorescent in the operating room and in the pathology department) will be sectioned into multiple slices at 2 mm to 3 mm intervals along their longest axis. Thereafter, all cassettes will be paraffin embedded. All lymph nodes will be analyzed after standard staining with hematoxylin and eosin.

Negative sentinel lymph nodes and fluorescent lymph nodes will be examined with further serial sectioning at 150 µm intervals and evaluated by standard hematoxylin and eosin staining.

To avoid the risk of bias with micrometastases being detected more frequently in fluorescent lymph nodes related to the higher number of examined fluorescent lymph nodes in comparison with nonfluorescent lymph nodes, a similar number of negative lymph nodes (nonstained or blue found afterward at pathology) will be examined in the same way as the fluorescent lymph nodes by serial section with standard hematoxylin and eosin staining.

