**Figure 1 figure1:**
[figure not shown]
Illustrations of the systemic sentinel lymph node hypotheses. In patients with small tumors, we expect to find a correlation between the blue sentinel lymph node and the systemic lymph node. In patients with large tumors, we expected to have a false negative blue sentinel lymph node and a true positive systemic lymph node. FI: fluorescence imaging; ICG: indocyanine green.

The primary objective of the SeLyNoFI study is to assess the feasibility of metastatic lymph node detection in colorectal cancer by ex vivo fluorescence imaging after intravenous administration of indocyanine green dye. In this study, we will evaluate the sensitivity, specificity, and accuracy of the technique for determining nodal status, both intraoperatively (entire fresh specimen imaging) and in the pathology department (fixed specimens).

The secondary objectives are to correlate the results of the fluorescent sentinel lymph node detection technique after intravenous injection of indocyanine green dye with sentinel lymph node detection by the standard blue dye technique, to study the link between the local lymphatic drainage pathway (classical tumor-draining sentinel lymph nodes) and the systemic pathway (systemic sentinel lymph nodes). Finally, we will evaluate the tumor-to-background fluorescence ratio of the primary colonic tumor.

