## Methods

### Study Design

The SeLyNoFI study is designed as a single-arm, 2-step (monomulticentric), academic, prospective observational-interventional study conducted by the Department of Surgical Oncology at the Institute Jules Bordet of the *Université Libre de Bruxelles* in Brussels. It will start as a monocentric, 2-stage (Simon procedure) study and will be followed by a multicentric study (among members of the International Research Institutes network) if the null hypothesis that the sensitivity of the indocyanine green–fluorescence imaging technique is lower than 60% (*p*_0_, sensitivity obtained by the classical blue dye technique improved by 10%) can be rejected based on the data generated in the monocentric study (*p*_1_, power calculated in case of a true sensitivity of 90%). To assess the feasibility of this technique, all cases will be included, even under conditions in which the technique might be expected to be unreliable (eg, long delay between injection of indocyanine green dye and fluorescence assessment). However, if the null hypothesis cannot be rejected after the monocentric phase, further development will be halted (Figure 2).

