### Population

#### First Step (Monocentric)

To determine the sample size of the study, we used the 2-stage Simon procedure (minimax design) [20]. The first stage requires a small sample size (n_1_) and determines the threshold r_1_ as the number of successes (ie, TP_1_, the number of true positives) above which the trial’s second stage can begin. If that number is not surpassed (TP_1_<r_1_), then the trial ends at the end of the first step.

Once the second stage has begun, the total sample size, including those already enrolled in stage 1, is defined (n_tot_=n_1_+n_2_), and the second threshold r_tot_ for the number of successes (TP_1_+TP_2_) is defined. If the total number of successes surpasses the threshold (TP_1_+TP_2_>r_tot_), the monocentric study can terminate, and the indocyanine green dye technique will be considered worthy of further evaluation in the multicentric study. If the number of successes is not surpassed after (TP_1_+TP_2_<r_tot_ for n_tot_ cases), then the trial will terminate, and the technique will be considered inadequate and abandoned.

With *p*_0_= 60% and a *p*_1_=90%, the sample size needed in the first stage is n_1_=8 (lymph node–positive N1 or N2) and the number of successes (true positive) to surpass is r_1_=5. The total sample size needed is n_tot_=17 (lymph node–positive patients) with a total number of successes r_tot_=14 (with α=.05 and β=.10). As the prevalence of patients with N1, N2, or N3 is estimated to be 50%, the number of patients needed for enrollment in stage 1 and 2 are about 16 and 34, respectively.

Based on the number of patients treated at the Institute Jules Bordet, the time necessary to execute this step is estimated to be 1 year.

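### Late-found fluorescent nodes are all examined intensively while late-found blue nodes are at most sampled, and passing the fixed 60% gate cannot by itself show improvement over blue dye

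*Protocol article*

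**What the plan says.** **Pathology.** The first paragraph of Pathology Examination gives late-found blue nodes the routine work-up: "Nonsentinel lymph nodes (including blue stained lymph nodes found afterwards) will undergo classic pathologic analysis (longitudinal bivalve section". For the other colour, "all fluorescent lymph nodes (found to be fluorescent in the operating room and in the pathology department) will be sectioned into multiple slices", at 2 to 3 mm. The second paragraph adds serial sectioning at 150 µm for negative sentinel and fluorescent nodes. The third paragraph, meant to limit bias, has a similar number of negative nodes, either unstained or blue found afterwards, serially sectioned too. The section on fluorescence imaging in the pathology department says that stained nodes of either colour found there do not count as sentinel nodes.

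**Benchmark.** Study Design sets the null sensitivity at 60%, described as the "sensitivity obtained by the classical blue dye technique improved by 10" percent. Passing the two-stage rule leads to the multicentric step.

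**Blue-dye data.** The Abstract plans sensitivity, positive predictive value and accuracy for both techniques. The secondary objectives and the Discussion plan to correlate them, and concordant nodes are recorded. Statistical Analyses lists patient-level sensitivity and positive predictive value, with subgroups by mucinous histology and by delay. The Figure 1 caption makes a prediction by tumour size: "In patients with large tumors, we expected to have a false negative blue sentinel lymph node and a true positive systemic lymph node".

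**The concern.** Late-found blue and late-found fluorescent nodes have the same non-sentinel status but are not searched equally hard. Small metastases come to light where the search is most intensive, so the set of patients called node-positive is partly shaped by the technique under study. A patient upstaged only through a fluorescent node enters the reference as a true positive for fluorescence and a false negative for blue.

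The only formal decision rule compares fluorescence with a constant derived from blue dye, although both dyes are applied to the same specimens. The Abstract makes comparison with blue dye an aim, and the Discussion hypothesises that systemic sentinel nodes represent invasion better than classical ones. If blue dye performs better here than the constant assumes, passing the gate says nothing about improvement over it. The listed subgroups also leave the tumour-size prediction unexamined.

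**Working it through.** **1. Work-up by type of node (Pathology Examination)**

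| Node | Sectioning before first H&E | Serial sectioning if negative |
|---|---|---|
| Green stitch, operating room | 2–3 mm slices | all |
| Blue stitch, operating room | 2–3 mm slices | all |
| Fluorescent, found in pathology | 2–3 mm slices | all |
| Blue, found in pathology | bivalve | only if drawn into the control sample |
| Unstained | bivalve | only if drawn into the control sample |

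The stitched nodes are treated alike; rows three and four are not. The control sample has no stated selection rule and could consist of unstained nodes alone. It balances fluorescent against non-fluorescent nodes in number, not fluorescent against blue.

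**2. Effect on the reference standard (upper bound)**

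Assume 50% node-positive prevalence (the article's figure), so node-negative patients equal node-positive ones in number. Assume further that a share u of the node-negative patients is upstaged only through fluorescent nodes, that each counts as a true positive for fluorescence and is missed by blue, and that the control sample finds nothing. With true sensitivity s:

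- fluorescence reads (s + u)/(1 + u)
- blue reads s/(1 + u)
- the artificial gap is u/(1 + u)

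With s = 0.60 for both:

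| u | Fluorescence | Blue | Gap (points) |
|---|---|---|---|
| 5% | 0.65/1.05 = 61.9% | 0.60/1.05 = 57.1% | 4.8 |
| 10% | 0.70/1.10 = 63.6% | 0.60/1.10 = 54.5% | 9.1 |
| 20% | 0.80/1.20 = 66.7% | 0.60/1.20 = 50.0% | 16.7 |

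**3. The gate as planned**

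Inputs from Study Design and First Step (Monocentric): null 60%; "power calculated in case of a true sensitivity of 90" percent; "with α=.05 and β=.10"; "the sample size needed in the first stage is n_1_=8"; "the number of successes (true positive) to surpass is r_1_=5"; 17 node-positive patients in total; final threshold 14. With k the total number of successes required,

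P(pass) = Σ over x = 6 to 8 of b(8, x, p) × P(Bin(9, p) ≥ k − x).

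- k = 14 (more than 13): 0.0436 at p = 0.60 and 0.9045 at p = 0.90. This is the minimax design for the stated error rates, so the sizes 8 and 17 reproduce.
- k = 15 (more than 14, as the text is written): 0.0123 and 0.762.

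The wording of the threshold is a separate matter, so both readings are carried below.

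**4. The gate when fluorescence is no better than blue**

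Take both at 75% (assumption).

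- k = 15 allows at most 2 failures, so stage 1 is always passed: 0.75^17 + 17(0.25)(0.75^16) + 136(0.25²)(0.75^15) = 0.0075 + 0.0426 + 0.1136 = 0.164.
- k = 14 adds exactly 3 failures, not all in the first 8 patients: (680 − 56)(0.25³)(0.75^14) = 0.174, giving 0.337.

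Over a range of common sensitivity, P(pass) for k = 14 and k = 15 is 0.192 and 0.077 at 70%, and 0.529 and 0.310 at 80%.

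**5. What a paired contrast could show**

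Exact McNemar test, two-sided 0.05, fluorescence at 90%. Blue sensitivity b and the dependence between techniques are assumptions. Independent errors give discordant probabilities 0.9(1 − b) and 0.1b; blue positives nested in fluorescent positives give 0.9 − b and 0.

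| Blue | Power, 17 patients | Power, 73 patients |
|---|---|---|
| 50% | 58–74% | over 99% |
| 60% | 34–40% | at least 98% |
| 70% | 11–13% | 82% to over 99% |
| 80% | under 3% | 31–75% |

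**The case against.** Much of the case on the other side stands, and it rules out four stronger readings that a reader might infer.

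- *Late-found blue nodes never get serial sections.* The third paragraph of Pathology Examination makes them eligible for the control sample. What remains is that they may be sampled, while every late-found fluorescent node is examined.
- *Every fluorescence-versus-blue contrast is biased.* Stitched nodes of both colours get the same work-up, and late-found nodes of either colour are not sentinel. The asymmetry reaches the operating-room sensitivity only through the reference standard. It bears directly on the sensitivity assessed in the pathology department, which Statistical Analyses also plans.
- *The paired data go unused.* Blue-dye accuracy, correlation and concordance are all planned. Statistical Analyses names no within-patient contrast, but an analysis plan that is not shown may supply one, and may also add a tumour-size split. Their absence from the article is not in itself an error.
- *The 60% gate is a superiority test.* A fixed benchmark is normal in a Simon design, and passing only sends the technique on to further study. Nothing in the article says that rejecting 60% will be reported as a gain over blue. The implied blue rate is itself ambiguous: 50% if the 10% is additive, 0.60/1.10 = 54.5% if relative. Subtracting either from the observed sensitivity is a reading that the article does not make.

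The low power at 17 patients also means that a paired test would be a poor replacement for the gate.

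**Conclusion.** The point holds in a limited form. The stated pathology rule favours the investigational technique among late-found nodes, and the control sample mitigates this without equalising fluorescent against blue. At 10% upstaging through fluorescent nodes only, the distortion is at most 63.6% against 54.5% from a common true 60%. The 10%, the common 60% and the counting rules are assumptions, and the figure ignores the control sample.

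The gate is sound as a screen for further evaluation, but passing it is not evidence of improvement over blue in these patients: with both at an assumed 75%, it is passed with probability 0.16 or 0.34 depending on how the threshold is read. The listed subgroups do not address the tumour-size prediction in Figure 1. This deserves correction before the comparison with blue is analysed; it does not undermine the feasibility objective.

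**What to change.** - Keep the Simon gate as the step 1 decision.
- For fluorescence versus blue, use only nodes stitched in the operating room (green versus blue). Define node-positive patients by first-pass H&E, and report serial-section findings separately as upgrading.
- In node-positive patients, report the paired 2×2 table and the difference in sensitivity with a 95% CI for paired proportions. Give the exact McNemar test as support, mainly at the 73 patients of step 2.
- Add pT1–2 versus pT3–4 beside the listed subgroups.
- Base any statement that fluorescence is better than blue on this comparison, not on rejection of 60%.
- Reconcile the first and third paragraphs of Pathology Examination on how late-found blue nodes are examined, and state how the control sample is selected.

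The analysis changes use data already planned for collection. The cost is wide intervals in step 1, where the pT split is also small. First-pass H&E removes the serial-sectioning difference, but 2–3 mm slicing against bivalve section of late-found nodes remains and should be acknowledged.

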### Semiquantitative Image Analysis of Fluorescence

Recorded videos will be used to calculate the fluorescence intensity of all primary tumors and analyzed lymph nodes. Regions of interest will be drawn over the primary tumor and lymph nodes and over the adjacent background tissue. Fluorescence intensity, expressed in arbitrary units of lymph nodes and tumor background, will be measured with the IC-Calc (version 2.0, Pulsion Medical Systems SE). Finally, tumor-to-background fluorescence ratios will be calculated for each lymph node and for the primary tumor. Fluorescence imaging videos of fresh (nonfixed) and fixed lymph nodes in cassettes will be used for tumor-to-background fluorescence ratio calculations. For primary colon calculations, tumor-to-background fluorescence ratio will be calculated using intraoperative videos on the entire fresh operative specimen after exposure of the colon.

All specimens will be imaged under standard conditions with the near-infrared camera by the same person. The findings of these images will be correlated with definitive pathological reports of the lymph nodes.

### Statistical Analyses

The sensitivity of the first step (monocentric study) will be evaluated for patients where the fluorescence evaluation has been performed just after the colectomy in the operating room and also afterward in the pathology department.

Sensitivity and positive predictive value will be computed at the patient level, on the total, and in different subgroups based on histology of the tumor (nonmucinous versus mucinous adenocarcinoma) or delay between injection of indocyanine green dye and fluorescence examination.

Upgrading percentage will be calculated on fluorescent lymph nodes with negative pathological examination. Concordance between visual scale and tumor-to-background fluorescence ratio will be evaluated with the kappa statistic.

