Recently, indocyanine green–fluorescence imaging has emerged as a potential technique for the detection of sentinel lymph nodes after peritumoral injection [9-11]. The preliminary results of studies [12-15] using peritumoral injection of indocyanine green dye for sentinel lymph node detection in colorectal cancer were encouraging, but we recently reported the results of a pilot study [16] which were disappointing in terms of accuracy and sensitivity.

New approaches are thus required. Recently, we published our observations on using fluorescence imaging after intravenous injection of indocyanine green dye to detect lymph node metastatic deposits both ex vivo and in vivo in colorectal cancer [17]. We confirmed these findings in a recent retrospective study [18] evaluating 12 patients who underwent colonic resection, for peritoneal metastasis detection after intravenous injection. Moreover, we observed that primary colonic tumors were more fluorescent than surrounding tissue upon fluorescence imaging after intravenous injection of indocyanine green dye.

Therefore, we hypothesized that ex vivo fluorescence imaging after intravenous injection of indocyanine green dye could represent a new approach for improving nodal staging through detection of fluorescent lymph nodes on the operative specimen. Furthermore, we hypothesized that these lymph nodes, identified after intravenous injection of indocyanine green dye and defined as systemic sentinel lymph nodes, when compared with classical anatomical tumor-draining sentinel lymph nodes, could represent a lymph node subset that is more sensitive to nodal invasion, thus serving as a more appropriate target for advanced histopathological analyses. The pathophysiological mechanism is 3-fold: first, in patients with large tumors, involved lymph nodes will be more fluorescent; second, in patients with small tumors, the fact that primary colonic tumors accumulate indocyanine green dye and that the dye is progressively cleared from the tumor by lymphatic drainage should allow the lymph node draining the tumor to be highlighted (Figure 1); and third, regarding the enhanced permeability and retention effect, we can consider that inflamed or reactive lymph nodes accumulate more indocyanine green dye and become more fluorescent [19]. This is very interesting considering that reactive lymph nodes present more risk to be invaded and are thus a key target for extensive histopathological analyses [19].

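### The upgrading percentage is defined on fluorescent nodes with no comparison rate, although control nodes and negative blue sentinel nodes are serially sectioned too

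*Protocol article*

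**What the plan says.** Under Pathology Examination, nodes that are neither sentinel nor fluorescent "will undergo classic pathologic analysis (longitudinal bivalve section"). Fluorescent and blue sentinel nodes get more: "Negative sentinel lymph nodes and fluorescent lymph nodes will be examined with further serial sectioning at 150 µm intervals". The authors see that this unequal search could favour fluorescent nodes and add a safeguard. It opens with "To avoid the risk of bias with micrometastases being detected more frequently in fluorescent lymph nodes" and provides that "a similar number of negative lymph nodes (nonstained or blue found afterward at pathology) will be examined in the same way".

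The statistic for this work is in Statistical Analyses: "Upgrading percentage will be calculated on fluorescent lymph nodes with negative pathological examination". The same section lists patient-level sensitivity and positive predictive value, subgroups by histology and by delay from injection, and a kappa for visual scale against tumor-to-background ratio. It names no upgrading rate for any other node group and no comparison between groups.

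The idea that upgrading bears on is in the Introduction. Compared with classical tumor-draining sentinel nodes, the fluorescent nodes "could represent a lymph node subset that is more sensitive to nodal invasion, thus serving as a more appropriate target for advanced histopathological analyses".

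**The concern.** Serial sectioning examines more tissue, so it can find deposits that the first look missed in a node of any staining. The article recognises this, which is why it adds control nodes. A safeguard of this kind works only if the control result is set beside the fluorescent result, and the statistic as worded does not do so.

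The Introduction's hypothesis, repeated in the Discussion, is comparative, and its named comparator is the blue sentinel node. Negative blue sentinel nodes are serially sectioned as well, yet they have no upgrading rate either. A reader given one percentage could credit fluorescence with a yield that comes from the sectioning.

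**Working it through.** **Stated figure.** The article gives no expected upgrading rate, node count or precision for upgrading, so there is nothing to reproduce. The check compares the passages and then illustrates the consequence with assumed rates.

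**Which serially sectioned groups have a stated upgrading rate**

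| First-look-negative group | Serially sectioned? | Upgrading rate stated? |
|---|---|---|
| Fluorescent nodes | yes | yes |
| Non-fluorescent controls (unstained, or blue found later) | yes | no |
| Blue sentinel nodes | yes | no |

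**What one rate can show.** Let *s* be the share of comparable non-fluorescent nodes that serial sectioning upgrades, and *e* the excess associated with fluorescence. The planned figure is U_F = *s* + *e*. One number cannot separate two unknowns. The control rate U_C estimates *s*, so D = U_F - U_C estimates *e*.

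**Illustration (assumed, not from the article).** Take 100 fluorescent and 100 control nodes, treated as independent, with 10 fluorescent nodes upgraded.

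Wilson interval for U_F: [p + z²/2n ± z√(p(1-p)/n + z²/4n²)] / (1 + z²/n), with p = 0.10, n = 100, z = 1.96.
- Centre: (0.10 + 0.0192)/1.0384 = 0.1148
- Half-width: 1.96 × √(0.0009 + 0.000096)/1.0384 = 0.0596
- Interval: 5.5% to 17.4%

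Newcombe interval for D, from the Wilson limits (l, u) of each group:
- lower = D - √[(p_F - l_F)² + (u_C - p_C)²]
- upper = D + √[(u_F - p_F)² + (p_C - l_C)²]

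For 10% in both groups, the root is √(0.0448² + 0.0744²) = 0.087, so D = 0 (-8.7 to 8.7 points).

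| Control upgrading | Planned figure (95% CI) | D in points (95% CI) |
|---|---|---|
| 0% | 10% (5.5 to 17.4) | +10 (4.2 to 17.4) |
| 2% | 10% (5.5 to 17.4) | +8 (1.3 to 15.6) |
| 5% | 10% (5.5 to 17.4) | +5 (-2.6 to 13.0) |
| 10% | 10% (5.5 to 17.4) | 0 (-8.7 to 8.7) |
| 20% | 10% (5.5 to 17.4) | -10 (-19.9 to about 0) |

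The middle column never changes, while the quantity of interest runs from +10 to -10 points. With 50 nodes per group and 10% in both, D = 0 (-12.7 to 12.7).

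These intervals ignore clustering. Correlation among a patient's nodes widens the interval for each rate. Taking both groups from the same patients can partly offset that for the difference. The real intervals need a patient-level method.

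**The case against.** The best defence is that this is a condensed article and its full protocol and analysis plan are not shown. The sentence on upgrading does not exclude a control figure, and collecting controls to avoid bias suggests that a comparison is intended. Upgrading is also not among the listed objectives. As a descriptive yield of extra sectioning in fluorescent nodes, the percentage is valid.

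Much of this stands, and it rules out several stronger readings that a reader might infer:
- *Upgrading is computed only in fluorescent nodes, so the controls go unused.* The text does not say only. Control results also enter the pathology reports with which imaging findings are to be correlated, and could alter a patient's nodal status.
- *The controls are a non-random, convenient sample.* The article gives no selection rule, so this is not established.
- *The figure will be positive whatever fluorescence does.* It can be; in a small sample it may be zero.
- *The study's main conclusion is undermined.* The go/no-go rule counts true-positive patients and does not use the upgrading percentage.

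The defence does not remove the core point. The article does not leave this statistic open: it names the nodes on which it is computed, two sections after explaining why those nodes alone would be a biased basis. Neither correlation with pathology reports nor "Sensitivity and positive predictive value will be computed at the patient level, on the total, and in different subgroups" supplies an upgrading comparison.

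**Conclusion.** The point holds in a limited form. The stated upgrading percentage has no comparison rate, although two suitable groups are serially sectioned under the same plan. It describes yield in fluorescent nodes and cannot, alone, show that fluorescence marks the better nodes for advanced histopathology.

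Its size in this trial is unknown. Under the assumed 10 of 100, the same reported 10% fits differences from +10 to -10 points as control upgrading runs from 0% to 20%. The logic needs only that serial sectioning can upgrade some non-fluorescent nodes, which is the possibility the article's own safeguard addresses. The matter deserves correction but does not threaten the primary decision.

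**What to change.** Amend Statistical Analyses to report:
- the upgrading percentage, with numerator and denominator, in fluorescent nodes, in serially sectioned non-fluorescent controls and in negative blue sentinel nodes;
- the fluorescent-minus-control and fluorescent-versus-blue-sentinel differences, each with a 95% CI that allows for clustering of nodes within patients, for example by a patient-level bootstrap, and with a stated rule for nodes that are both blue and fluorescent;
- the number of patients moved from node-negative to node-positive by each group.

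Preferably also state that controls are picked at random, within patient, from the eligible negative nodes.

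One caution belongs beside the control comparison. Fluorescent and blue sentinel nodes are cut at 2 to 3 mm at first look, whereas controls are bivalved, or loaded unsectioned if under 4 mm. Controls may therefore be upgraded more often simply because they were searched less at first. The blue sentinel comparison does not have this imbalance.

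The cost is a few sentences and a short analysis, since the slides are already planned. The first step enrols only about 34 patients, about 17 of them node-positive, so intervals will be wide and should be presented as descriptive. With few upgraded nodes, an elaborate regression model is not advisable.
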